## Abstract

**Background:**

The goal of personalized medicine (PM) is to provide tailored diagnostics and therapies for individual patients, primarily in oncology. However, significant regional disparities exist in its implementation. The Deutsches Netzwerk für Personalisierte Medizin (DNPM; German Network for Personalized Medicine) project aims to harmonize and network the implementation of PM in Germany.

**Methods:**

The DNPM project is evaluated as a Hybrid Type 3 implementation study using a non-randomized, modified stepped-wedge design. Twenty-one university hospital sites across Germany will transition from standard, non-harmonized care to a harmonized personalized medicine intervention at different time points, based on administrative readiness indicated by certification. The primary outcome is change in patient management due to molecular tumor board (MTB) decisions, assessed on three tiers using prospectively collected primary data entered by clinical staff: (1) number of patients with access to an MTB, (2) proportion with revised diagnostic or therapeutic recommendations, and (3) proportion with implemented changes. Therefore, the study aims to include 4,807 patients (intervention group: 3.507). A mixed-methods approach is employed to evaluate further aspects of the implementation process including patient and staff satisfaction, perceived quality of care, and the degree of harmonization and collaboration within the network. Health economic outcomes include health-related quality of life, healthcare utilization costs, and intervention-related costs.

**Discussion:**

The study's wide range of outcome parameters and mixed-methods approach yield robust results for implementation insights. A limitation of the study design is the lack of a clear cutoff for transitioning from the control to the intervention group and the lack of randomization. Additionally, the health economic evaluation is limited by the absence of health insurance claims data, as no insurance company is involved in the project.

**Trial registration:**

This trial is registered with the German Clinical Trials Register (DRKS) under the trial number DRKS00031622 (registration date: 23 May 2023)

## Introduction

### Background and rationale

Personalized medicine (PM) leverages rapid advancements in high-throughput diagnostics, functional imaging, and data processing, including artificial intelligence, to provide patients with targeted treatments that minimize side effects. In oncology, the principles of molecularly stratified medicine are being extensively researched across all types of tumors and are already being applied in patient care (1–3). This has led to the segmentation of tumor entities into increasingly smaller patient groups that, despite having the same entity, differ significantly in their molecular structure and therefore require different treatments. Consequently, this has resulted in highly individualized treatment approaches, which must rely on an evidence-based, harmonized decision-making process that can only be achieved through the collection of individual disease and therapy data.

To support these advancements, four university hospitals in Baden-Württemberg (BW) (Tübingen, Freiburg, Ulm, and Heidelberg) have each established a Center for Personalized Medicine (ZPM), included as a center in the state hospital plan by the Baden-Württemberg Ministry of Social Affairs in 2019, aiming to integrate PM principles (such as the systematic integration of biological, genetic, environmental, and lifestyle variability into prevention and treatment strategies, with the aim of improving individual patient outcomes and reducing adverse effects) into the healthcare system. Although the centers initially focus on oncology, they are designed to adapt to other disease areas. A key element is the systematic collection of data from treatment contexts and linking it with data from sources such as gene sequencing, omics technologies, or imaging, to improve individualized treatment. This approach depends on harmonized diagnostics and treatment decision-making.

The implementation of the ZPM concept in BW, with a focus on molecular oncology, is based on significant preliminary work from precision oncology networks, including the Molecularly Aided Stratification for Tumor Eradication Research (MASTER) program of the German Cancer Research Center (DKFZ). This initiative developed key elements and standards, such as cross-entity and cross-location molecular tumor boards (MTBs), standardized documentation of longitudinal clinical data, grading of genetic variant evidence, and multisite molecularly stratified clinical trials, among other translational research projects (4, 5). Furthermore, the National Genomic Medicine Network (nNGM) for lung cancer, established in 2016 across all 13 comprehensive cancer centers (CCCs), has contributed to the harmonization of diagnostics, documentation, and MTB recommendations for lung cancer (6).

Building on these efforts and the existing structures within CCCs, the ZPM-BW initiative, in collaboration with health insurance providers in BW [Allgemeine Ortskrankenkasse (AOK) and Verband der Ersatzkassen (vdek)], has developed a specialized concept that establishes shared quality standards and integrates ZPM principles into routine care. Quality criteria have been defined across the following areas:
Structural and organizational setup of the ZPM and its networkDecision-making processes in MTBsIT systemsDocumentationQuality managementBased on data harmonization processes introduced within ZPM-BW, all CCCs in Germany will now be enabled to integrate their structures and processes into the emerging DNPM. In this project, the new processes and structures outlined above will be implemented at CCCs across Germany, establishing further ZPMs. By the end of the project's funded period, a nationwide, digitally interconnected, interoperable, and patient-centered network will be in place to translate PM into patient care (7). This will considerably increase the amount of data, utilize the experience of 13 top centers, and significantly improve the possibility of comprehensive care in personalized oncology. To exchange this data (e.g., demographic patient data, diagnoses, treatment courses, genetic and pathological phenotype, recommendations from the MTB, and follow-up on these recommendations, as well as outcome data), the DNPM is creating a nationwide data platform, the dnpm:DIP, to enable secure, pseudonymized sharing of phenotypic, genomic, and imaging data between centers. This decentralized system supports quality control by national health insurers and facilitates data-driven decision-making in MTBs and patient inclusion in molecularly stratified trials (7).

To guarantee a comparable quality of innovative and interdisciplinary care across all centers, the DNPM has set up a certification system for the ZPM in the DNPM with the German Cancer Society [Deutsche Krebsgesellschaft (DKG), OnkoZert] and thus serves as a blueprint for clinical implementation.

### Specific project goals at the micro-, meso-, and macro-levels

Micro-level: On the micro-level (individual), the DNPM will introduce and further develop standardized quality criteria and digital documentation procedures, including the following:
Inclusion criteria for MTBsMolecular diagnostics and bioinformatic analysis methods (shared genetic core data set, ring trials for the analysis pipeline)Evidence determination for therapy recommendationsDigital documentation (interoperable, standardized data models)Imaging as follow-up monitoring (digitally, structurally, and machine-readable documented)Meso-level: Establishing ZPMs at all sites involves setting up fundamental structures (ZPM office and board) and integrating these into the respective university hospital and CCC. A major milestone is the development of a regional care and data network that ensures cost-efficient implementation and patient flow management and prevents uncontrolled diffusion of PM, multiple treatments, and over-provision of care.

Macro-level: Networking the ZPMs into DNPM governance structures and sustainability plans will be developed in consultation with all partners, and a DNPM steering board will be established with equal representation from each ZPM. A network-wide database (dnpm:DIP) will be created in collaboration with existing national infrastructure initiatives, which will be essential for the utilization of patient data, especially as patients are increasingly stratified into smaller cohorts.

Through these structured documentation and data exchange efforts, a robust evidence base will be built, serving as the foundation for more efficient clinical trials and improved patient outcomes in PM.

### Objectives

#### Specific objectives for primary analysis

Increase the number of patients for whom standardized access to the new form of care of personalized diagnostics and therapy is possibleIncrease the chance of treatment recommendationsIncrease actual implementation of treatment recommendations

### Specific objectives for secondary analysis

Patients can benefit from the standardization of PM in ZPM regarding access to individualized therapy.The ZPM specialist concept BW can be transferred to other locations.Increased communication between the individual ZPMs provides added value for the efficiency of patient care.

## Methods: participants, interventions, and outcomes

### Intervention description

All participating centers will undergo a certification process as oncological centers in accordance with the requirements set by the German Cancer Society (8). Centers will transition to the intervention group once they meet the DNPM criteria and receive a positive audit result. In the intervention group, patients will be treated according to DNPM standards, which encompass quality-assured molecular diagnostics and evidence-based treatment recommendations within interdisciplinary MTBs. The therapies initiated at these sites may vary individually in terms of timing, duration, and type.

The DNPM standards encompass ongoing quality control measures, the standardization of diagnostics, bioinformatics, MTBs, referrals for genetic counseling and imaging, and clinical decision-making based on harmonized evidence levels. See Appendix 1 for a summary of the dimensions of certification. The standardized and registered components of ZPM include a uniform and organized documentation of MTB decisions (approximately 40 harmonized parameters), coordinated clinical and genomic datasets (each containing over 200 parameters), consistent follow-up and response documentation, and a structured process for off-label treatment applications that has been agreed upon with the medical service and government health insurances. A nationwide network in the field of personalized oncology is established following these core measures:
**Micro-level:** improvement of evidence-based treatment recommendations in the MTB**Meso-level:** quality-assured, harmonized operation of ZPM (Centers for Personalized Medicine) at CCC locations**Macro-level**: establishment and use of a digitally connected PM registry (using the example of the Baden-Württemberg ZPM network) to improve treatment recommendations

### Trial design

The current study employs a Hybrid Type 3 design, evaluating the overall implementation while monitoring and collecting data on the clinical intervention's effects on important outcomes (9). Using a mixed-methods approach, the study integrates quantitative measurements and qualitative data collection across multiple stakeholder groups, including patients and healthcare staff. In addition, key structural and process parameters will be documented over time, and a health economic evaluation will be conducted. The study design is based on a modified stepped-wedge approach: The participating centers transition at different time points from a control condition—characterized by site-specific, non-harmonized PM practices—to the intervention condition, which reflects harmonized PM procedures. While this approach resembles the classical stepped-wedge design in its sequential rollout across sites, it deviates in one important aspect: The timing of the transition is not randomized. Instead, it is determined by administrative and organizational readiness. Specifically, a center enters the intervention group on the date documented in its certification form, which confirms that essential steps toward PM harmonization have been implemented. The certification criteria align with the standards set by the German Cancer Society (Deutsche Krebsgesellschaft) (8).

### Timeline of the study

Participant recruitment was completed on 30 September 2024. Data collection is expected to be finalized by the end of November 2025, with results anticipated in January 2026.

### Sample size

The study aims to recruit a total of 4,807 patients, including 3,507 in the intervention group and 1,300 in the control group. The following assumptions underlie the sample size estimation: For nine newly established ZPMs (centers), two centers would be acceptable as dropouts. At least four existing centers in BW are considered unlikely to drop out, and seven newly initiated ZPMs serve as the basis for the sample size estimation. The new centers will contribute to controlling/intervening patients before/after initiation as ZPM, while the existing ZPM will only have intervention patients. This approach, inspired by the stepped-wedge design, has already been successfully used in several projects funded by the Innovation Fund (10). An average stay of 6 months in the control phase is assumed. It is estimated that each comprehensive cancer center (CCC) will have between 300 and 500 patients with PM, resulting conservatively in 1,300 control patients. This is compared with an estimated 3,500 ZPM patients from existing ZPM and those newly implemented during the study period. With these numbers, ignoring the cluster effect, differences of approximately 5% can be detected in the chi-squared test (Type I error 5% two-sided) with a power of >80% (exactly 86%) and differences of 7% with >90% (exactly 96%) power. Assuming a variance inflation due to cluster effects of 2, differences of 7% can still be detected with 85% power, and with very high cluster effects of 4 or 6, differences of 10% or 13% can be detected with 85% power.

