### Outcomes

A central element is the primary endpoint at the patient level (micro-level), which is divided into a three-tiered endpoint and allows conclusions about the benefits of the intervention. Tier 1 includes the frequency of access to the new form of care; Tiers 2 and 3 encompass the development and implementation of therapy proposals. The quantitative evaluation is supplemented by a quantitative patient survey using validated questionnaire instruments and a health economic assessment. In addition to quantitative data collection, interviews with patients are conducted to capture patient understanding of and expectations regarding personalized medicine. Overall, the development and enhancement of structures and processes in centers for personalized medicine (ZPM) is documented through standardized self-report questionnaires (see Appendix 2), as well as interviews and focus groups. This also specifically captures the exchange and knowledge transfer between ZPMs, as well as the extent to which an exchange of harmonized data has taken place. A complete list of the measures used in the quantitative and qualitative process evaluation, as well as secondary patient-related endpoints (clinical: response, PFS, OS, toxicity, patient questionnaires, and health economic measures), is presented in Table 2. A design diagram further elaborating on the data collection time points can be found in Appendix 3.

**Table 2 T2:** Primary and secondary endpoints and data collection.

Level	Evaluation	Primary endpoint	Time point	Instrument
Micro-level	Quantitative evaluation	Change in patient management based on the decision of the tumor board (assessed on three tiers):		Based on a quantitative questionnaire filled out by staff on site *(included in the provider questionnaire)*
		Tier 1: number of patients admitted to the tumor board	T0 = day of initial presentation at the tumor board)	
		Tier 2: proportion of patients with changed diagnostic strategy and/or therapy recommendation due to the decisions of the tumor board	T1 = day of therapy decision	
		Tier 3: proportion of patients with an actually implemented changed diagnostic strategy and/or therapy	T2 = day of the first therapeutic intervention	
		Secondary endpoints		
Micro-level	Quantitative evaluation	Clinical data of patients treated in the MTB • Response • Progression-free survival • Overall survival • Toxicities	event-driven	*Included in the provider questionnaire*

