		Patient satisfaction and quality of life of patients treated in the MTB • Satisfaction • Quality of life	At study enrollment, 2–3 months after enrollment, and 5–6 months after enrollment	• Modified questionnaire instrument based on the PSCC-G instrument • Established questionnaire instruments for disease-specific quality of life, EQ-5D-5L, and EORTC QLQ-C30 *(included in the patient questionnaire)*
		Health economics • QALYs • Total costs (healthcare costs, intervention costs) • ICER	5–6 months after enrollment	• EQ-5D-5L • Modified FIMA questionnaire • Controlling the data of participating university hospitals • Survey of centers *(included in patient questionnaire)*
	Qualitative evaluation	Patient-level survey: • Understanding and attitude toward personalized medicine • Qualitative assessment of the implementation processes • Expectations regarding care provided by the personalized medicine services (ZPMs)/the decentralized personalized medicine (DNPM) • Perceived care before and during treatment with ZPMs/DNPM • Costs incurred in the context of personalized medicine care	At a later stage in the project	Semi-structured interviews with patients
Meso-level and macro-level	Process evaluation (quantitative)	Perspective of staff from centers for personalized medicine (ZPMs): • Degree of standardization of processes • Establishment of new coordination processes at the medical or professional level (e.g., expert committees) • Implementation and structural costs (costs incurred from transitioning to ZPM/DNPM) • Process costs (ongoing costs before ZPM, or of the individual ZPMs) • Exchange/knowledge transfer between ZPM • Exchange of harmonized data • Presence of interconnected data structures (e.g., completeness, quality) • Exchange of harmonized data between the ZPMs • Communication and decision-making structures and processes	• T0: at the time of certification • T1: at an intermediate stage in the project • T2: at a later stage in the project	Quantitative questionnaire based on the certification forms at the center, participation in meetings of the MTB working group, and analysis of the working group’s meeting minutes *(organizational structure and process survey)*

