### Participant timeline

Table 3 shows the participant schedule throughout the intervention period.

**Table 3 T3:** Participant schedule.

Specification of data collected	Participant schedule			
	Enrolment	2–3 months post-enrolment	5–6 months post-enrolment	Close-out
Time point/assessment	T0	T1	T2	T3
Study participation				
Eligibility screen	X			
Informed consent	X			
Allocation	X			
Clinical data collection				
Socio demographics	X			
Diagnose	X	X	X	
(Further) therapies in the last 3 months outside the MTB recommendation	X	X	X	
MTB recommendations		X	X	
Follow-up on MTB recommendations		X	X	
Scheduled end (follow-up completed after 5–6 months)				X
Reason for premature end				X
Patient questionnaire				
Socio demographics	X	X	X	
Living situation	X	X	X	
Financial Situation	X	X	X	
Social support	X	X	X	
EQ-5D-5L (health-related quality of life)	X	X	X	
EORTC QLQ-C30 (disease-related quality of life)	X	X	X	
FIMA (Utilization of health services)	X	X	X	
Patient satisfaction	X	X	X	
Patient interviews				
Understanding, expectations, and attitudes toward PM, perceived care		X	X	

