### Data collection and management

#### Quantitative evaluation

The primary endpoint contains three tiers. At Tier 1, the primary endpoint is the number of patients who receive an indication-driven, standardized access to the new form of care—personalized diagnostics and therapy—defined as access to the MTB. For this endpoint, a standardized data collection instrument will be developed to document both the original procedure and the newly implemented one, including the extent of the changes made (e.g., additional molecular diagnostics and therapy). The new procedure will be based on predefined, evidence-based criteria established by the ZPM network in BW. At Tier 2, it will be assessed for which patients the diagnostic process or diagnostic interpretation was significantly changed. Among this group, Tier 3 evaluates the proportion of patients for whom the changes ultimately led to treatment within the framework of personalized medicine. These changes may also include recommendations for genetic counseling, which—although not directly involving therapy or additional diagnostics—represent a modification in patient care.

Secondary clinical endpoints will be assessed continuously during the study: Adverse events (AEs) and serious adverse events (SAEs) will be recorded as they occur, and overall survival (OS) and progression-free survival (PFS) will be recorded every 6 months (T4–T8) until the end of the observation period, with a minimum follow-up of 6 months and an average follow-up of 12 months.

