These expected changes reflect the underlying hypothesis that harmonization and standardization of personalized oncology care will enhance the integration of MTBs into clinical workflows and improve outcomes for patients. However, we have to take into account that harmonization is a complex process and implementation is not done on a certain date. Thus, in secondary analyses, we will exclude patients in the last 3 and 5 months before certification from the control group, and in an additional secondary analysis, we will analyze the time trend in centers that were newly certified, correcting for the time trend in centers that had been certified already at the beginning of the project. AEs and SAEs are expected to remain within acceptable limits, indicating good tolerability. Additionally, we expect improvements in OS and PFS, among patients receiving targeted therapies based on molecular tumor profiling. These outcomes would support the clinical value of the intervention in routine care.

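### Most control patients would reach their 5–6-month assessment after their centre is certified; the planned 3- and 5-month exclusions reduce this but do not reliably remove it

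*Protocol article*

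**What the plan says.** Under Trial design, "a center enters the intervention group on the date documented in its certification form". The Sample size section adds: "An average stay of 6 months in the control phase is assumed". Only the newly initiated centres supply control patients.

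Table 3 places allocation at enrolment and closes the schedule with "Scheduled end (follow-up completed after 5–6 months". Follow-up of MTB recommendations is recorded at 2–3 and 5–6 months. Table 2 sets satisfaction and quality of life "At study enrollment, 2–3 months after enrollment, and 5–6 months after enrollment"; FIMA follows the same schedule in Table 3. OS and PFS run longer, "with a minimum follow-up of 6 months and an average follow-up of 12 months".

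For the primary endpoint, Table 2 ties Tier 1 to first presentation at the board, Tier 2 to the therapy decision ("T1 = day of therapy decision") and Tier 3 to the first therapeutic intervention.

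The quantitative analysis section recognises that harmonization is gradual and plans secondary analyses: "we will exclude patients in the last 3 and 5 months before certification from the control group". A further secondary analysis compares the time trend in newly certified centres with that in centres certified from the start.

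**The concern.** A patient's scheduled follow-up is about as long as the control phase is expected to last. A control patient enrolled in month 4 of a 6-month control phase has the 5–6-month assessment 3–4 months after the centre has switched.

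This matters because part of the intervention acts after the board has decided. The Intervention description lists follow-up and response documentation and a structured route for off-label applications among the standardized components. Certification can therefore change whether a recommendation is carried out, and how that is recorded, in patients still counted as controls. The outcomes at stake are Tier 3 where implementation comes after certification, and the 5–6-month patient-reported outcomes, QALYs and costs. The likely direction is a smaller difference between the arms.

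The article does not discuss control follow-up that runs past certification. Its exclusion windows are justified by adoption before certification, and both end short of the latest scheduled visit at 6 months.

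**Working it through.** **Inputs from the article.** Control phase L: 6 months on average. No distribution is given, and "The participating centers transition at different time points from a control condition", so lengths may differ. Final assessment F: 5–6 months after enrolment, midpoint 5.5. Exclusions e: 3 and 5 months. Planned groups: 1,300 control and 3,507 intervention.

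**Assumptions.** Even enrolment at the same rate in every centre; visits spread evenly over their windows; 300–500 patients per centre read as per year; outcome rates near 50% for power.

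**The plan's own figures first.** Seven centres × 0.5 year × 300 to 500 = 1,050 to 1,750 controls; 1,300 corresponds to 1,300 / 3.5 ≈ 371 per centre-year. Power for 5 points without clustering is 86.9% (86.2% with continuity correction), against 86% stated. Both are consistent. The article gives no figure for controls followed past certification.

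**Share of controls whose final visit falls after certification.** A control crosses if enrolled in the last F months of the phase:

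- no exclusion: Σ min(L, F) / Σ L
- after excluding the last e months: Σ max(0, min(L, F) − e) / Σ max(0, L − e)

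With every L = 6:

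- none: 5.5/6 = 92% (5/6 = 83% to 6/6 = 100%)
- e = 3: 2.5/3 = 83% (67–100%), with 1,300 × 3/6 = 650 controls left
- e = 5: 0.5/1 = 50% (0–100%), with 1,300 × 1/6 ≈ 217 left

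Scenarios averaging 6 months, F = 5.5:

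| Phase lengths (months) | No exclusion | e = 3 | e = 5 |
|---|---|---|---|
| all 6 | 92% | 83% | 50% |
| 3, 4, 5, 6, 7, 8, 9 | 34/42 = 81% | 62% | 20% |
| 0, 2, 4, 6, 8, 10, 12 | 28/42 = 67% | 44% | 12.5% |
| half 2, half 10 | 7.5/12 = 63% | 36% | 10% |
| 1, 1, 2, 3, 6, 11, 18 | 23.5/42 = 56% | 29% | 8% |

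Since min(L, F) cannot exceed F, 92% is the ceiling at F = 5.5 for any set of phases averaging 6 months.

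**Share of control follow-up time after certification, equal phases.** Expected post-certification time is E[(F − e)²] / (2(6 − e)), divided by the mean follow-up of 5.5. With F uniform on 5–6, the variance is 1/12:

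- none: (5.5² + 1/12)/12 = 2.53; 2.53/5.5 = 46%
- e = 3: (2.5² + 1/12)/6 = 1.06; 1.06/5.5 = 19%
- e = 5: (0.5² + 1/12)/2 = 0.17; 0.17/5.5 = 3%

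**The 2–3-month visit.** With equal phases, 2/6 to 3/6 = 33–50% of controls cross. After the 3-month exclusion none do, whatever the phase lengths.

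**Precision for a 7-point difference (no clustering / design effect 2).** 1,300 controls: 99% / 86%. 650 controls: 91% / 64%. 217 controls: 52% / 29%. (The article states 96% for 7 points without clustering; the difference has no bearing here.)

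**The case against.** The strongest reply is that an assessment date is not an exposure. Patients enter at first presentation to the board, and Tiers 2 and 3 are tied to dated events rather than to the 5–6-month visit. A late questionnaire from a patient whose diagnostics and board decision came before certification can properly measure the consequences of control care. This stands in large part. What remains exposed is what happens after the decision, and the article does not say how often that falls after certification. Some patients are also treated outside the centres, which may weaken any effect of certification on them.

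A reader might infer that control outcomes are largely produced under the intervention and that the exclusions leave the problem in place, so that agreement with the main result would be false reassurance. The documents do not support this. Even with equal phases, less than half of control follow-up time (46%) is post-certification, and the exclusions bring it to 19% and 3%. A graded shift across the analyses would itself be informative. If the effect were immediate and implementation spread evenly over follow-up, a true 7-point Tier 3 difference would appear as 7 × 0.54 = 3.8 points, rising to 7 × 0.81 = 5.7 and 7 × 0.97 = 6.8. The article supports neither condition, so these figures are illustrative only.

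The article also openly acknowledges the blurred transition and plans a time-trend analysis. That analysis corrects for trends over calendar time; it does not separate a control patient's follow-up before and after certification. Nor does the arm variable that changes over time: it changes by centre, while a patient has one allocation and one binary outcome per tier. Which patient date defines the arm may be settled in an analysis plan not shown, and its absence is not held against the article.

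**Conclusion.** The point holds in limited form. On the article's planning figures, a majority of controls reach the final assessment after certification in every scenario tried: about 92% (83–100%) with equal 6-month phases and even enrolment, and 56–81% with unequal phases at the 5.5-month midpoint. The figure of about 9 in 10 is near the ceiling and should not be quoted without its condition.

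Tier 1 is not affected, and Tier 2 only where the decision falls after certification. Tier 3 is affected where implementation falls after certification. The 5–6-month patient-reported outcomes, QALYs and costs may be diluted towards zero by an amount the documents do not let one estimate.

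The two exclusions, chosen for a different reason, reduce the exposure substantially. The 3-month exclusion already leaves the 2–3-month visit clean. Neither reliably clears the 5–6-month visit, since the 5-month exclusion does so only if that visit falls at 5 months exactly. With equal phases the 5-month exclusion also leaves too few controls (about 217) to settle the question.

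**What to change.** 1. Pre-specify a comparison of Tier 3, the patient-reported outcomes and FIMA at the existing 2–3-month assessment in both arms, excluding controls enrolled in the last 3 months before certification. On the enrolment schedule of Tables 2 and 3, no control visit then falls after certification. Tie this analysis to that schedule, because other sections time some questionnaires from the start of therapy.
2. Add a Tier 3 sensitivity analysis that counts implementation in controls only up to certification, with the same time window applied in the intervention arm.
3. Report the share of control follow-up lying after certification next to every 5–6-month result.

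Widening the exclusion to 6 months is not a remedy: with 6-month control phases it leaves no controls.

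The change is to analysis wording and uses assessments and event dates already planned. The cost is precision and scope. With equal phases the clean comparison keeps about half of the controls (about 650), lowering power for 7 points from 99% to 91% without clustering and from 86% to 64% at a design effect of 2. It also sees implementation over a shorter window, so it should accompany the 5–6-month analysis rather than replace it.
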